**List of acronyms**

CCPW Community Child Protection Workers

CDP Community Development Project

CHW Community Health Worker

CRENAS Centres de Réhabilitation Nutritionnelle Ambulatoire pour les Malnutris Aigus Sévères [Outpatient Nutritional Recovery and Education Centers]

CRENI Centres de Réhabilitation Nutritionnelle Intensif [Inpatient Nutritional Recovery and Education Centers]

CT Cash Transfer

CTC Community Therapeutic Care

EU European Union

HAZ Height-for-Age Z-score

IFPRI International Food Policy Research Institute

IRD Institut de Recherche pour le Développement [French National Research Institute for Sustainable Development]

MASSN Ministère de l’Action Sociale et de la Solidarité Nationale [Minister of Social Action and National Solidarity]

MDBAJEJ Ministère du Développement à la Base, de l’Artisanat, de la Jeunesse et de l’Emploi des Jeunes [Minister of Grassroots Development, Crafts, Youth, and Youth Employment]

ODK Open Data Kit

PHND Poverty, Health, and Nutrition Division

PPCM Programme de prise en charge de la Malnutrition [Integrated Community Case Management of Childhood Illnesses and Undernutrition (ICCM-Nut)]

SC School Cafeteria

SSN Social Safety Net

UMR Unité Mixte de Recherche [Joint Research Unit]

UNICEF United Nations Children's Fund

USP Unité de Soins Périphérique [Peripheral Care Unit]

WHZ Weight-for-Height Z-score

# **Introduction**

The Community Development Project financed by the World Bank in Togo is implementing an approach to social welfare via two social safety net (SSN) programs, namely: (a) school meals for approximately 38,000 primary school students in the country’s most vulnerable areas, and (b) labor-intensive public works employing 25,000 young people in rural areas. In light of these programs’ successes, and in an attempt to sustain Togo’s ongoing efforts to realize the establishment of social welfare policies that address the needs of the most vulnerable populations, the World Bank and the Togolese government opted to renew funding for the PDC, while adding an element dedicated to a conditional cash transfer pilot project (PDCPlus). This pilot project, in partnership with the Togolese government (MASSN and MDBAJEJ) and UNICEF, will launch in June 2014 in five districts in the Kara and Savanes regions and will last for 30 months. It will coordinate with a childhood malnutrition healthcare program carried out by regional health services in these districts and financed by UNICEF, and will incorporate certain flexible conditionalities (encouraged, not mandatory). The project is aimed at pregnant women and mothers of children under 24 months old; its objectives are to encourage behavior conducive to the protection and well-being of beneficiary children, and to improve their nutrition and health.

The current protocol concerns the impact evaluation of the cash transfer pilot project. It attempts to determine the effectiveness of cash transfers in conjunction with the program dedicated to preventing and treating acute malnutrition through changes observed in the following indicators: nutritional status, diet, child welfare, care, and morbidity; the protocol also aims to assess the program’s impact pathways. This evaluation will be conducted by the Joint Research Unit Nutripass of IRD, in scientific partnership with the PHND (Poverty, Health, and Nutrition Division) of IFPRI.

A process evaluation and program cost analysis are also planned, but these are addressed in other protocol documents.

# **II. The cash transfer project**

## **2.1. Objectives and standards**

The principal objective of the cash transfer (CT) project in Togo is to improve impoverished communities’ access to social safety nets. This project will also enable both testing the implementation of a cash transfer program and evaluating how the government might employ such a tool in the long term.

In an effort to improve the expected outcomes of this cash transfer project, a decision was made to test it in coordination with another community-based project, whose functioning already involves state services. This coordination should allow for the completion of a package of existing services to the benefit of the target group. From the public actions matching this description, the Integrated Community Case Management of Childhood Illnesses and Undernutrition program (hereinafter abbreviated as “ICCM-Nut”), implemented by the Ministry of Health and financed by UNICEF and the EU, was chosen. The ICCM-Nut is carried out by the Nutrition Service (Ministry of Health) in the Kara region (365 villages) and the Savanes region (200 villages). The ICCM-Nut’s objectives are to prevent malnutrition among children 59 months old and younger, and to provide treatment for severely malnourished children.

UNICEF provides personnel training and resources essential to treating severely malnourished children at Inpatient Nutritional Recovery and Education Centers (hereinafter abbreviated as “CRENI”) and Outpatient Nutritional Recovery and Education Centers (“CRENAS”), as well as necessary equipment and medicine. At the village level, the system established consists of a community health worker (CHW), who is assisted by a support committee often made up of volunteer mothers. The CHW organizes monthly meetings to track the growth of children up to 59 months old. When a child shows mild signs of malnutrition, they are placed into a group of “vulnerable infants”, who benefit from closer monitoring and dietary counseling. Severely malnourished infants who present no medical complications are cared for by CHWs at the community level, in order to avoid prolonged stays away from home at CRENAS facilities. However, any child exhibiting signs of severe malnutrition and experiencing medical complications is referred to the closest CRENI facility, in order to undergo a “nutritional recovery” fortified by medical and dietary treatment.

Hopefully, a synergy will develop between the ICCM-Nut and the cash transfer project, which would permit:

***-Promoting behaviors conducive to children’s welfare and well-being:***

The CT project has established some flexible conditionalities to encourage essential positive behaviors that promote the welfare and well-being of children. These behaviors include: obtaining a birth certificate, sending siblings to school when they are of age, keeping children living at home (as opposed to foster care), and pregnant women and mothers’ attendance at the monthly growth-tracking meetings. Educational gatherings centered around these themes and childrens’ rights will be organized. This complementary relationship between welfare and health/nutrition creates a “knowledge package”, whose purpose is to encourage mothers to invest in their children’s well-being and futures.

***-Improving the nutritional status of beneficiary children:***

The CT project will strongly encourage mothers’ participation in educational meetings regarding nutrition and hygiene, organized regularly by CHWs. As a result of mothers’ slightly increased purchasing power (via cash transfers), it is expected that they will be better able to implement the guidance they receive and to devote more resources to buying essential food items, thus providing a balanced diet for their children.

***-Better care for severely malnourished children:***

Community child protection workers (CCPWs) will conduct regular home visits, during which they will enlist and encourage mothers and guardians to attend children’s growth-tracking meetings; this regular and increased attendance will greatly aid CHWs in monitoring children closely and early detection of severe malnutrition necessitating medical care. Including these especially vulnerable children as CT beneficiaries will facilitate more comprehensive care for malnourished children and limit potential relapses.

## **2.2. Intervention areas**

The CT project will be concentrated in the two northern regions (Kara and Savanes) and some of the villages under ICCM-Nut supervision. The ICCM-Nut is active in 365 villages in the Kara region and 200 in the Savanes region. These localities, called CTC (“Community Therapeutic Care”) villages, were identified by UNICEF based on their isolation and distance from the closest peripheral care unit (UPS). Because the available financial resources will not allow for all CTC villages to be covered, the following refined targeting process will be used:

-Choosing the poorest districts, with the most concerning nutritional indicators, in both regions. The chosen districts are as follows: (a) Kpendjal and Oti from the Savanes region, and (b) Dankpen, Doufelgou, and Kéran from the Kara region.

-Using random selection to identify the villages to be covered within these districts.

The localities chosen for the pilot phase are very poor, remote villages, with little to no access to basic social services (for example, the closest healthcare unit is typically at least five kilometers away).

## **2.3. Terms of transfers**

### **2.3.1. Targeting beneficiaries**

Taking into consideration the extreme levels of poverty in targeted villages and the insignificance of the inequality between residents therein, a universal targeting method based on children’s ages made it possible to reach those most at risk for malnutrition. Additionally, the impact of pregnant mothers’ nutrition on the healthy development of their pregnancies and their children was taken into consideration, and led to the inclusion of all women pregnant for at least three months in the beneficiary group. Community members deemed this inclusion method to be extensive and equitable, and judged it would preserve villages’ social cohesion. Thus, in each targeted village, cash transfer recipients will be women who have been pregnant for at least three months and the mothers and guardians of all children up to 24 months old. This reflects the concept of “1,000 days”, which is considered worldwide to be a window of opportunity for intervention and combating undernourishment. Furthermore, any mother or guardian of a child under five years old and suffering from severe acute malnutrition (with or without medical complications) will be systematically included. In polygamous households, each mother of an eligible child will benefit from cash transfers through the eligibility of said child. In cases where two children (not twins) with the same mother both qualify as beneficiaries, only the eligibility of the youngest child will be taken into consideration. In cases of the death of an eligible mother, the child’s caretaker (as chosen by the family) will be registered in her place. A miscarriage or the death of an eligible child voids a mother’s eligibility.

The following exceptions, however, shall be granted:

- A mother of twins 24 months old or younger will receive two cash transfers;
- A mother who, in addition to her own eligible child, is the guardian of an eligible child whose mother is deceased shall be considered equivalent to a mother of twins.

### **2.3.2. Transfer values**

The monthly disbursement is 5,000 CFA francs per eligible child, and is paid for a minimum of 12 months and a maximum of 30 months. This decision will permit the project, over the course of at least three years, to reach a significant number of beneficiaries (an estimated 8,000 children are eligible) while testing the functionality of the system in place.

### **2.3.3. Conditionalities**

The selected conditionalities will be flexible and non-exclusive, and should help communities adopt behaviors conducive to the well-being and welfare of children. Mothers who meet these conditionalities will receive a small bonus at the end of the program. The conditionalities for each child are as follows:

- Possession of a birth certificate or an attestation to the ongoing procuration of a civil

status document

- Mother/guardian’s attendance at educational meetings concerning childhood needs

- Mother/guardian’s regular attendance at monthly childhood growth-tracking meetings

- At least four antenatal consultations (for pregnant mothers)

- Keeping children under 15 years old living at home (as opposed to in foster care)

- Primary school attendance for all children of age in the household, in order to avoid

child trafficking and exploitation

Community agents in charge of the project’s implementation will provide each household with the necessary accompaniment (information, referrals, administrative procedures, etc.) for the purpose of promoting the adoption of these proposed conditionalities.

## **2.4. Mechanisms of action**

There are multiple ways in which this program may act upon childhood well-being and development. Leroy et al. recently described the pathways by which cash transfers, conditional or not, can theoretically improve children’s nutritional status, by developing a model of causal pathways. This model has been adapted for the current project in order to identify how the latter might influence children’s diet, health, and nutritional status.

[figure not shown]

Figure 1 : Mechanisms of conditional cash transfers’ potential influence on nutritional status (from Leroy et al., 2009^[[1]](#footnote-1)^)

# **Evaluation of the cash transfer program**

## **3.1. Specific evaluation objectives**

The objective is to evaluate the impact of cash transfers in conjunction with the ICCM-Nut, through documenting and analyzing the changes in several indicators relevant to children: diet, nutritional status, morbidity, and child welfare. This objective will also include an analysis of beneficiary households’ use of funds received and an analysis of the project’s impact pathways.

## **3.2. Methodology**

### **3.2.1. Approach**

The framework for analyzing the program’s impact will be experimental: all villages in the study area (*n*=162) will be randomly assigned either to an intervention group or a control group. Over a period of 24 months, cross-sectional surveys of children aged six to 29 months and their mothers will be conducted in these villages; one survey will take place before the program begins (hereinafter referred to as “baseline”) and the second will be conducted at the program’s end (hereinafter referred to as “endline”). A difference-in-differences analysis will permit both to determine whether situational evolution between the baseline survey and the endline survey differs significantly between the intervention group and the control group, and to conclude what impact is attributable to cash transfers and/or the flexible conditions with which they are associated.

Rationale for selected impact evaluation design:

1. ***Repeated cross-sectional vs. longitudinal design*.** We propose to use a repeated cross-sectional survey design rather than a longitudinal design primarily because our previous experience has shown that usual delays in program roll-out and full implementation can have profound effects on the evaluation study cohort (e.g. children aging out of the “window of opportunity” for maximum nutritional impact of the intervention – see point 2 below), making the cohort unusable for assessing impact on age-sensitive outcomes such as child feeding practices or stunting. Additional constraints of longitudinal designs include the logistical complexity and related additional cost of tracking individual children over time, compared to sampling children of a given age in a repeated cross-sectional design. However, given that our team has extensive experience with both types of designs, we are open to discussions with UNICEF and the World Bank regarding alternative designs.
2. ***Age range of children included in evaluation samples.*** The assessment of the impact of nutritional interventions on child anthropometry (as well as other outcomes) should consider the age at which assessments should be made to detect the greatest difference between intervention and comparison areas. Evidence suggests that (1) the *longer* children are exposed to early nutrition inputs (within the first 1,000 days, or from conception to the child’s second birthday) and (2) the *earlier* they are exposed within this period, the greater the impact will be.

Furthermore, achieved height-for-age is likely to be greatest between intervention and control children in the age period *after* the peak age of growth faltering (i.e., after 18-24 months of age).

The logic behind investments made from conception until the child’s second birthday is that they are progressive and cumulative; hence our ability to detect a significant impact on anthropometry particularly, will be greatest among those children who were exposed to interventions in the entire period preceding the peak age of growth faltering. This means that the age at which impact on anthropometry should be assessed is dependent on (1) the child’s age at the onset of their exposure to program interventions, (2) the total duration of exposure to interventions within the 9 to 24 month target age-focus, and (3) the peak age of growth faltering.

As impact on intermediary outcomes such as complementary feeding indicators will also be measured, we have to make sure that the corresponding age group (i.e. children > 6 months of age) is well represented in our sample.

We are applying these principles to define the exact age group for whom to assess impact on feeding and nutritional outcomes, taking into account demographic and logistical considerations.

1. ***Duration between baseline and endline surveys*.** Although the proposed pilot program will last 30 months, the need to ensure that baseline and endline assessments are conducted at the same time of the year (and thus minimize the impact seasonality has on key indicators of interest) means the duration between baseline and endline assessments should be 24 months apart (allowing extra time for preparation and post-survey analysis).

Given the considerations outlined above, the duration of the program (30 months), and logistical considerations about sample sizes at particular age ranges, we propose sampling children six to 29 months of age at endline (two years after the baseline). Sampling the six-to-29-month age range is a compromise that takes into account a minimum program exposure of 12 months and first exposure to the program no later than six months of age. These criteria are based on the assumption that the main program intervention of cash transfers will begin immediately following the baseline survey and continue for 30 months, although at the time of the endline survey no child would have been exposed to the program for more than 24 months. Any delay in the start of cash transfers will have an impact on the age range of children to be sampled.

Table 1 below illustrates the age of first exposure, and duration of exposure of children of different ages, assuming a period of 24 months between baseline and endline surveys, and an immediate start to the cash transfer program after the baseline survey:

Table 1 : Program exposure of sample age range at endline

| **Age (mo)  at Endline** | **Age (mo) at First Exposure to Program** | **Age (mo)at Last Exposure to Program** | **Total Program Exposure (mo)** |
| --- | --- | --- | --- |
| 0 | -6 | 0 | 6 |
| 6 | -6 | 6 | 12 |
| 12 | -6 | 12 | 18 |
| 18 | -6 | 18 | 24 |
| 24 | 0 | 24 | 24 |
| 30 | 6 | 24 | 18 |
| 36 | 12 | 24 | 12 |
| 42 | 18 | 24 | 6 |
| 48 | 24 | 24 | 0 |
| 54 | N/A | N/A | 0 |
| 60 | N/A | N/A | 0 |

Extensive information will be collected at the levels of villages, households, mothers, and children, in order to:

**i) determine the program’s impact on several pertinent results**

- Diets of children and their mothers
- Care and welfare of children
- Morbidity
- Anthropometry of children

**ii) understand the ways in which the program works**

- Women’s use of funds received
- Tracking of household expenses
- Use of health services
- Women’s roles and decision-making power within the household
- Behavioral changes relative to questions around children’s nutrition, hygiene, health, and welfare
- Household food security

**iii) describe the analysis’s context and take into account potential confounding factors**

- Village characteristics (facilities, equipment, etc.)
- Household demographics and socioeconomic characteristics
- Jobs and education levels of heads of households and women
- Hygiene
- Economic shocks endured by households

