**Household non-food expenses:** These will be calculated based on the following items: lodging (rent, maintenance), cooking fuel source, electricity, water, health and education, hobbies, personal hygiene, clothing, shoes, vehicles, beauty care services, and communication. All of these expenses will be scaled to a monthly figure, which will then be weighted according to the household’s adult equivalent number as described above.

**Household food insecurity access scale (HFIAS):** The HFIAS scale permits a holistic look at households’ food insecurity, based on consequences and feelings stemming from recent experiences with food insecurity and strategies developed to deal with it. This instrument is inspired by the Radimer-Cornell scale, developed and employed in the United States within the framework of its federal food assistance programs, and has been adapted for use in developing countries following several tests and validation experiences. Scores are calculated based on responses to nine questions that address the various dimensions of food insecurity in order of increasing importance, according to current recommendations. Each response is marked between 0 (a “no” response) and 3 (1 to 3, depending on how frequently the household experiences the situation in question). The reference period comprises the prior month. The final score will thus range between 0 (indicating a food-secure household) and 27 (maximum food insecurity). Additionally, households’ experiences with the most severe consequences place them in one of four categories (food-secure and slightly, moderately, or severely food-insecure).

**Household economic shock:** Some households may experience economic shock during or just before the program that affects the family environment and, consequently, children. It is therefore invaluable to glean this information retrospectively in the context of this evaluation. If indeed a household experiences economic shock during the program, it may explain any possible lack of positive program impacts.

**Hygiene and sanitation:** Household hygiene can have a large impact on children’s health and nutritional status. We will employ spot checks to estimate the cleanliness of the property and its inhabitants, which have proved to be an efficient, non-intrusive, quick, and affordable approach. A short questionnaire on household sanitation (toilets, wastewater systems, and trash) will supplement this method.

❖ **PERTAINING TO MOTHERS**

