**Mother’s characteristics:** This component consists of mothers’ civil statuses, education levels, and revenue sources.

**Schedule and child care:** Mothers’ schedules will be examined, as they can directly influence dietary practices and child care. The time mothers spend taking care of their children (meals, games, healthcare) will be observed with particular interest.

**Mother’s status, autonomy, and decision-making power:** This component will assess women’s household autonomy (particularly with regard to finances), the treatment they endure within the household (abuse, insults, anxieties, etc.), their involvement in sensitization meetings and social/community networks, and their decision-making power relative to issues of diet, health, education, family planning, and children’s rights within their households.

**Use of health services and attendance at informational sessions:** This component will take into account pregnancy history, household situations during the course of pregnancy (reduced work, improved diet, etc.), the number of pre- and post-natal consultations, birth setting and external help received, and mothers’ involvement in training sessions on children’s health, diet, and rights.

**Mother’s knowledge, attitudes, and practices (“CAP”):** The program aims to improve mothers’ knowledge bases in order to impact their dietary practices and their conduct relating to the caretaking, hygiene, nutrition, and rights of their children. After adjusting for certain variables such as education and socioeconomic levels, changes in the CAP between the baseline and endline surveys will be examined to evaluate the program’s impact pathways. The CAP questionnaires will be adapted to the content of the monthly information sessions planned in the project.

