**Hygiene pathway (through spot checks)**

- Child’s hygiene: cleanliness of hands, face, hair and clothes
- Mother’s hygiene: cleanliness of hands, face, hair and clothes
- Yard’s sanitary conditions: animal feces, waste

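### Hygiene is classed both as a potential confounder and as an intermediate outcome, and the knowledge, attitudes and practices analysis adjusts for a socioeconomic index that the transfers could change

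*Protocol*

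**What the plan says.** Section 3.2.1 sorts the information to be collected into three lists by purpose. List iii serves to describe context and "take into account potential confounding factors". It contains hygiene, along with "Household demographics and socioeconomic characteristics" and "Economic shocks endured by households".

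Hygiene also has other roles:

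- List ii of section 3.2.1, on how the program works, includes "Behavioral changes relative to questions around children’s nutrition, hygiene, health, and welfare".
- Section 3.2.5, on mothers' knowledge, attitudes and practices (CAP), says the program aims to affect dietary practices and "their conduct relating to the caretaking, hygiene, nutrition, and rights of their children".
- Section 3.2.6 has, among the intermediate outcomes, an entry that begins "Hygiene pathway (through spot checks". It covers the child, the mother and the yard.
- For the household hygiene item, section 3.2.5 says: "We will employ spot checks to estimate the cleanliness of the property and its inhabitants".

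On adjustment, the protocol has one explicit sentence, in the CAP paragraph of section 3.2.5: "After adjusting for certain variables such as education and socioeconomic levels, changes in the CAP between the baseline and endline surveys will be examined". The purpose given is to evaluate impact pathways. The socioeconomic index is described earlier in that section. It is built from housing quality, utilities, household objects, productive assets, livestock and land.

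The impact model in section 3.2.6 contains phase, group and their interaction, and no other term.

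**The concern.** In a randomised comparison, a variable that the intervention is designed to change is not a confounder of the intervention's effect. It is an outcome, and possibly a mediator. Adjusting for it takes out whatever part of the effect passes through it. If the variable and the outcome share unmeasured causes, adjustment can also introduce bias in either direction. The adjusted coefficient is then no longer the total effect of assignment.

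The design sharpens this. In a longitudinal study one could adjust for a household's own baseline value. Here different children are sampled at each survey, so an endline household has by design no linked baseline record. Adjusting at household level for hygiene or wealth therefore means using, for the endline sample, values recorded after the program has run.

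The stake is direct for the CAP analysis, where the adjustment is written down. For other outcomes it is conditional: an analyst who took list iii as the covariate list would condition on one of the protocol's own outcomes.

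**Working it through.** No stated figure is in dispute, so the check is mainly a comparison of roles, with a short calculation of exposure.

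1. **Hygiene.** Section 3.2.1 list iii gives it a context or confounder role. Section 3.2.1 list ii makes it a mechanism, section 3.2.5 (CAP) a target of the program, and section 3.2.6 an intermediate outcome. The instruments overlap: the household item in section 3.2.5 uses spot checks of property and people, and the pathway outcome uses spot checks of child, mother and yard. The household item adds a short questionnaire on toilets, wastewater and trash, which the pathway outcome does not name. The conflict is therefore clear for spot-check hygiene and not shown for the sanitation questionnaire.

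2. **Socioeconomic level.** Several components of the index (household objects, productive assets, livestock) can be bought. Section 2.1 itself expects that greater purchasing power will help mothers act on the guidance they receive. For the practices part of CAP, household means therefore lie on the protocol's own causal path.

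3. **Exposure when endline values are recorded.** Inputs are 5,000 CFA francs per month per eligible child (section 2.3.2) and the exposure by age in Table 1 (section 3.2.1). I assume one payment per month of exposure and an immediate start, as Table 1 does. Total = 5,000 × months of exposure.

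| Age at endline (months) | Exposure (months) | Transfers (CFA francs) |
|---|---|---|
| 6 | 12 | 60,000 |
| 12 | 18 | 90,000 |
| 18 | 24 | 120,000 |
| 24 | 24 | 120,000 |
| 30 | 18 | 90,000 |

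The range for the sampled ages is 60,000 to 120,000, and 120,000 is the ceiling.

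4. **Adjustment in the impact model.** Section 3.2.6 fits an intercept, phase, group and phase × group, and takes the interaction as the effect. Nothing from list iii enters. The same section says the method already takes pre-existing group differences into account.

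5. **Mechanism, as illustration only.** In a linear model with no unmeasured common cause of mediator and outcome, adjusted effect = total effect × (1 − s), where s is the share running through the adjusted variable. The protocol gives no value of s. Taking 0.20 as a total effect and assuming s = 10%, 25% or 50% gives 0.20 × 0.90 = 0.18, 0.20 × 0.75 = 0.15 and 0.20 × 0.50 = 0.10. At s = 0 nothing is lost. A simulation (300 data sets per share, 1,020 children per group and phase, independent observations) gave unadjusted interactions of 0.199, 0.196 and 0.197, and mediator-adjusted ones of 0.179, 0.147 and 0.096. This confirms the direction under those assumptions. It does not estimate what would happen in this trial.

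**The case against.** The strongest objection is that list iii is a data-collection list with two purposes. It does not say that any estimate will be adjusted for its items, and it does not say which items are context and which are confounders. Covariate choice is commonly left to a statistical analysis plan, which is not at hand. This stands in part: the protocol nowhere adjusts an estimate for hygiene. The conflicting classification is nevertheless in the protocol, and so is the adjustment of CAP for socioeconomic level.

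A reader might infer that the primary height-for-age estimate will be pulled toward zero and lose power. The protocol does not support that, because the stated model has no covariates. Any power figure would need both an invented mediated share and an assumption that adjustment leaves the standard error unchanged.

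A reader might also count economic shocks as a third such variable. The protocol does not support this either. Section 3.2.5 says shocks may come just before the program as well as during it, and uses them to help interpret an absence of impact. They are not listed as a pathway outcome.

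Two defences of the CAP adjustment deserve an answer. First, sample composition may shift differently between arms in repeated cross-sections, which is a fair reason to adjust. Variables the program cannot change can serve that purpose without conditioning on its consequences. Second, the analysis concerns pathways, so an effect net of wealth may be intended. That would be a different quantity from the total effect, with its own assumptions, and the protocol does not say it is the target.

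**Conclusion.** The point holds in a limited form. Spot-check hygiene cannot be both a confounder to take into account and an outcome of the program. The CAP adjustment for socioeconomic level would, for the endline sample, condition on an index recorded after about 12 to 24 months of transfers. Either could remove part of the program effect or bias it.

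The size is unknown, since it depends on how much of the effect runs through these variables and the documents do not give that. The CAP conclusion assumes that the adjustment uses household values from each survey, which is the natural reading of a repeated cross-section but is not stated. The variables are also collected at baseline, and those baseline values are not affected. As written, the primary analysis is untouched, so this is a modest correction to an intermediate analysis and to the classification of variables.

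**What to change.** - In section 3.2.1, take spot-check hygiene out of list iii and keep it as a mechanism and intermediate outcome. If the sanitation questionnaire is meant as context, name it separately.
- In the CAP paragraph of section 3.2.5, replace the adjustment for socioeconomic level with variables the program cannot change: district, child age and sex, adult education, and the village mean of the socioeconomic index at baseline.
- In section 3.2.6, state that any adjusted impact model follows the same rule.
- Keep economic shocks as descriptive or interpretive data.

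This changes wording only; no data item is added or dropped. The downside is a possible small loss of precision from giving up the household-level wealth index as a covariate. The index remains available for description and for pathway analysis.
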